### **11.2 Preparation, administration and dosage**

The method of preparation is similar to that of other infant formulas: addition of one level scoop of powder to the defined amount of water (boiled, lukewarm). For the feeding regimen, the official guidelines of the Ministry of Health are used. The frequency of formula feeding and the amount per feeding shall be ad libitum.

NUMICO as manufacturer of the products used during the study confirms that every quality control measure has been taken to assure correct composition and that the products have passed security clearance without objections. Expiry dates are imprinted on the packages / labels. However, normal shelf life can only be guaranteed if the product is appropriately stored:

Temperature: room temperature; avoid local heat (exposure to sun, radiators, etc.)

- Humidity: Close pack carefully after every use; do not store in rooms commonly known for higher humidity (kitchen, laboratories, etc.)
- Safety: to avoid misuse of trial material by inexperienced personal not involved in the study keep material at a respective safe place, if possible under lock and key.

The study starting formulas are indicated for feeding of full-term infants from birth onwards in cases where breast feeding is not possible, or the supply of breast milk is insufficient. For continuation of formula feeding beyond the infants' age of 6 months, follow-on formulas (FOF) are indicated.

No particular contraindications are defined. Contraindications, however, exists as for all cow's milk based infants formulas (cow's milk protein allergy, lactose intolerance, galactosemia, glucose-galactose-malabsorption).

### **11.3 Assessment of feeding compliance**

Compliance will be evaluated by using the food intake information as registered in the questionnaires.

In infants providing stool samples the intake of active formula can be checked by stool analysis, e.g. excretion of non-digested oligosaccharides.

### **11.4 Logistics of product supply**

NUMICO will supply the investigators with formulas on demand. At the study centres, the study formulas will be kept by the investigators, who agreed to store the formulas. A dispensary record of the study formulas issued and of any material returned will be kept. Unused formulas will be returned to Numico Research.

Study formula for 4-8 weeks will be given to the mothers in advance in case they started formula-feeding (partially or completely). Once they have started, sufficient supply of formulas is guaranteed by NUMICO for the first year of their infant's life.

### **11.5 Additional feeding recommendations**

Mothers are encouraged to breastfeed their infants for at least 4 months, preferably 6 months. The only substitute or supplement in case of insufficient breastfeeding is the randomised study formula. Parents are asked not to introduce weaning foods until their infants have reached the age of 4 months.

## **12. STUDY PROCEEDING IN DETAIL**

### **12.1 Enrolment**

Parents and their infants are potentially eligible if they seek medical attention with one of the participating hospitals/practitioners, e.g. for routine investigation at their infant's age up to 6-8 weeks. They will receive a detailed oral explanation about the purpose of the study and will be supplemented with an explanatory letter. Alternatively, mothers with healthy term newborn babies may be informed about the study (e.g. by a respective flyer containing also a contact telephone number), so that they actively can call back in case they would later on like to participate. If the parents or guardians have had enough time (at least some days) to think over to participate, infants up to the age of 8 weeks will be checked in a screening process for inclusion and exclusion criteria. If they fulfill the defined inclusion but not exclusion criteria and if the parents have signed the written informed consent form, they will be recruited.

### **12.2 Study groups**

If an infant has already been fed with at least one bottle of an accepted standard infant formula (cow's milk based formula with non-hydrolysed protein, no probiotics included), this infant will be recruited to the formula groups. Randomization between the two formula groups will take place immediately according to the prepared center-specific randomisation schedule (example see annex). If the infant is on full breastfeeding at study entry, it will be allocated to the non-randomised reference group. The latest possible inclusion day is at 8 weeks of age.

### **12.3 Per-protocol- and intention-to-treat-analysis**

The protocol foresees for the formula infants that they reach full formula feeding (FF) after 2 months of age at the latest and for the reference infants that they should stay on full breastfeeding (BF) for at least 4 months. Formula infants should cover all formula feedings during the study duration, i.e. till the infant's age of one year, with study IF/FOF. Deviations from this protocol will result in exclusion from the defined formula and breastfed groups with respect to the intended per-protocol-analysis (PP) after the study's end. Formula infants receiving breast milk beyond the age of two months will be evaluated in the per-protocol analysis as members of a mixed-feeding group (duration and estimated amount of breast milk intake will be recorded and statistically checked). For the intention-to-treat analysis (ITT), all infants having been randomised will be evaluated according to the initial group allocation.

[figure not shown]

## 12.4 Examination day 1

The most important examinations will be performed at 5 examination days throughout the study. Day of study entry is defined as *examination day 1*. Questionnaires will be filled in with data on the mother incl. age, demography and socio-economic status, occupation, general health, nutritional status, delivery etc. Data on the feeding pattern will be collected as well (basal questionnaire). The clinical examination of the infant will include anthropometry but to check for pre-existing illnesses which might interfere with the study also the assessment of atopic dermatitis and other skin symptoms (eczema, urticaria, others) as well as the assessment of respiratory (rhinitis, wheezing, etc.), GI tract (vomiting, colics, diarrhoea) and general symptoms (failure to thrive, irritability, food refusal).

## 12.5 Additional examinations in study subgroups

If the mother agreed that her child may provide stool samples for check of stool parameters on gut health and immune status throughout the study (examination day 2-5), faeces should be collected for later quantitative and qualitative bacterial analysis, pH measurements as well as analysis of faecal sIgA. Thus she will receive stool containers provided by NUMICO in which she should collect some fresh stool sample from her infant's first nappy of one day in the week before the next examination day (to be kept frozen and to be delivered by the mothers at next examination day). If the mother agreed that her child may also provide two times a small blood sample (2-3 ml) for more direct check of the immune status, a blood sample should be drawn for later analysis of biochemical blood/plasma parameters at the infant's age of 6 and 12 months. If infants are seriously ill or feverish at the time of the blood sampling or if they used antibiotics in the 2 weeks preceding the blood sampling (as indicated by the parents or concluded from the anamnesis), the sampling point can be postponed for up to 2 weeks.

## 12.6 Interviews

During the study period every 2-4 weeks parents are interviewed according to a structured protocol on the health status of their infants incl. feeding pattern, acceptance and tolerance, possible complaints etc. (follow-on questionnaire). To help accuracy of recall, mothers will be supplied at study entry with a diary containing record cards for feeding data (number of breast feeds, number and types (volume intake) of bottle feeds, number of juice and water feeds, number of solid feeds, dates of first bottle feed, last breast feed, first solid feed) as well as any symptom of their infants' illness and respective medication (see diary CRFs in the annex). The close contact to the mother (two-weekly in the study beginning up the infant's age of 4 months and four-weekly afterwards) will be guaranteed by a mix of personal contacts (visits in the clinic or at home) and intermittent telephone calls. At the end on each individual's study period all information gathered by home visits and telephone interviews should be retrospectively scrutinized by comparisons with the general practice records as this has been identified to minimise detection bias (Howie PW et al: Protective effect of breast feeding against infection. Br Med J 1990; 300:11-16). Whenever there is any doubt whether a disease episode fulfils the agreed definitions or not, a decision is to be made on the basis of information available by the local responsible clinician.

## 12.7 Further examination days

Repetition of the examinations and further sample drawings are planned for the infant's age of about 2 months (*examination day 2*, stools), about 4 months (*examination day 3*, stools), about 6 months (*examination day 4*, stools) and 12 months, i.e. at study end (*examination day 5*, stools and blood).

## 12.8 Vaccination / vaccination response

A uniform vaccination routine using HEXAVAC (to be provided by NUMICO) will be possible in the two Italian centers with vaccinations after 3, 5, and 11 months. The German center will also use HEXAVAC, however with another timing (2, 3, 4, 11 months, see study schedule overview below). The vaccination routine in The Netherlands and Switzerland differ from that according to country specific regulations regarding vaccination against Hepatitis B. The measurements of the immune status at examination day 5 (12 months) will include the measurement of the antibody response to the specific type of vaccination in the subgroup of HEXAVAC vaccinated infants having provided a blood sample.

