## **6.4 Possible confounding factors**

### **6.4.1 Obstetric, medical and social data**

- Maternal factors: age, parity, social class, height, smoking habit, marital stage, puerperal illness, previous medical illness
- Paternal and social factors: age, social class, number of rooms in the house, living conditions (urban / rural), smoking habit
- Infant factors: sex of child, date of birth (season!), birth weight, gestational age, mode of delivery (vaginally / caesarean section), Apgar score, neonatal jaundice, other illness before study entry, immunisation, number and age of siblings, illness in siblings, form of child care (home care, group care, day care centre)

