## 10.4 Randomisation

Randomization to one of the two formula groups will be performed directly after study entry of those mothers who have fed their infants at least one bottle of infant formula. Randomization will be performed stratified according to center. I.e., for each center a separate randomization list will be provided. All other potential confounders, such as obstetric, medical or social characteristics, will be checked and adjusted for in the final data analysis.

Time-balanced randomization will be performed with the software RANCODE (IDV, Gauting; seed numbers randomised by reaction time) with a random permuted block size of 4 so that after 4 infants each the same number of infants per formula group is reached. By this procedure the time influence (season etc.) is evenly distributed between the randomised group. An example of a randomization table is given in the annex.

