## 14. STATISTICAL ANALYSIS

### 14.1 Basic statistical procedure

Given the reasonably large sample size employing parametrical methods assuming a Gaussian distribution will be appropriate allowing for parametrical tests. If necessary, logarithmic transformations of skewed parameters are performed, e.g. for number of illness days.

The first step in the analysis will be a crude comparison between the two formula groups 1 and 2 testing the group effect (different formula) for

- quantitative variables by analysis of (co-)variance (ANOVA/ANCOVA)
- qualitative variables by Fisher exact test / Chi-test
- time-related variables (e.g. "time to infection") by percental frequency curves according to Kaplan-Meier functions / Mantel-Cox log-rank test

One example is an analysis of variance with two groups (T-test) with the number of febrile episodes per child as the dependent variable and type of supplementation as a categorical independent variable. Another example is a Kaplan-Meier curve / Mantel-Cox log-rank test of the percentage of infants without infection throughout the study.

[figure not shown]

The second step is a series of univariate analyses to identify confounders by testing the possible influence of characteristics of the infants on the outcome parameters (to be expressed as odds ratio (OR) and 95% confidence intervals (CI)). Variables considered as potential confounders are, e.g., gender, birth weight, number of siblings, attendance to daycare, smoking in household, duration of breastfeeding, etc.

The third step is a multivariate analysis to identify interaction variables, i.e. confounders which interact with exposure (feeding active formula or placebo).

The final analysis is aiming at simultaneous control of possible confounders and interaction variables by multiple regression analysis with stepwise variable selection to achieve a model that is parsimonious (has only few variables) but maximizes the proportion of the explained variance across study groups. Stepwise procedure:

- baseline model including exposure and core variables,
- stepwise introduction of two-way interaction terms involving exposure (p value to enter 0.05),
- elimination of variables not involved in significant interactions in the multiple regression model (change in exposure odds ratio < 5%).

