### **14.3.1 Interval data**

Inter-group comparisons will be performed for all interval data at any measurement point by using the analysis of variance (ANOVA) / T-test (if necessary to perform non-parametric tests -> Kruskal-Wallis test / Wilcoxon-Mann-Whitney U-test). In case of significance of the multiple group comparison, single group comparisons will be performed as post-hoc tests according to Fisher (if necessary to perform non-parametric tests -> Wilcoxon-Mann-Whitney-U-test).

For baseline adjustment, comparisons will be calculated not only using the raw data but also data differences (e.g. data at examination day 2 and 3 minus data at examination day 1) to account for individual variances.

Whenever needed, logarithmic transformation of data will be performed for homogenisation of variances prior to statistical analysis.

Within-group comparisons (e.g. examination day 3 versus day 1) will be conducted using the paired T-test (if necessary to perform non-parametric tests -> Wilcoxon-signed rank test).

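### The 12-month HEXAVAC antibody comparison holds three-dose and four-dose infants, but its stated tests omit centre, which fixes the schedule: some lost precision, no bias

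*Protocol*

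**What the plan says.** Section 12.8 (Vaccination / vaccination response) sets two HEXAVAC schedules. The two Italian centres have "vaccinations after 3, 5, and 11 months. The German center will also use HEXAVAC, however with another timing (2, 3, 4, 11 months"). Italian infants therefore receive three doses before the 12-month visit and German infants four. The Dutch and Swiss centres follow national rules.

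The same section then describes the 12-month immune assessment as including "measurement of the antibody response to the specific type of vaccination in the subgroup of HEXAVAC vaccinated infants" who provided blood. It does not split that subgroup by country or number of doses. Section 6.2 lists vaccine antibody titres as a secondary parameter.

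On allocation, section 10.4 states: "Randomization will be performed stratified according to center". The sentence that follows promises checking and adjustment for the remaining confounders, meaning those other than centre.

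On analysis, section 14.1 begins: "The first step in the analysis will be a crude comparison between the two formula groups 1 and 2 testing the group effect". It names ANOVA/ANCOVA for quantitative variables without naming covariates. Its examples for the later modelling are: "Variables considered as potential confounders are, e.g., gender, birth weight, number of siblings, attendance to daycare, smoking in household, duration of breastfeeding, etc". For interval data, section 14.3.1 states: "Inter-group comparisons will be performed for all interval data at any measurement point by using the analysis of variance (ANOVA) / T-test", with rank tests as the alternative. Centre is not mentioned anywhere in section 14. Section 6.4.1 does include vaccination among the possible infant confounders: "other illness before study entry, immunisation, number and age of siblings".

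**The concern.** Within the HEXAVAC subgroup, knowing the centre means knowing the schedule. The number and timing of doses may well affect the 12-month titre, so the protocol itself gives a reason to expect titres to differ between centres. It also randomises within centre. Yet the tests it states for this outcome compare the two formula groups as if all infants came from one population.

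What is at stake is precision. Any difference in mean titre between three-dose and four-dose infants is counted as residual noise, which widens the interval for the formula effect and lowers power. How much depends on how far apart the two schedules are. The point concerns one secondary parameter, measured only in infants whose parents consented to blood sampling.

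**Working it through.** **The plan's own figure.** There is no power statement for the antibody comparison. The only power figure (10.5) is for the primary outcome: 250 per group, difference 1, SD 3.5, giving 93% one-sided and 89% two-sided. Recomputed with the noncentral t distribution, these are 93.9% and 89.0%. That calculation is sound but does not bear on titres.

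**Inputs from the protocol.** Three HEXAVAC centres, two Italian and one German (12.8). Randomisation by centre in permuted blocks of 4 (10.4). Alpha 0.05 (14.3), taken as two-sided because the hypothesis in section 5 sets no direction for titres.

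**Assumptions, because the protocol gives no values.** Italian share p = 2/3 (equal numbers from the three centres), varied from 1/2 to 4/5. Schedule shift k = 0.25, 0.5 or 1.0 within-schedule SD. Formula effect set so that a test including centre has 80% power.

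**Formulas.** With two schedules in proportions p and 1 − p, leaving centre out adds v = p(1 − p)k² to a within-schedule variance of 1. If the arms are exactly balanced within centre, the difference in means does not itself carry the shift, but the test's standard error is too large by √(1 + v). Hence:

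- power = 1 − Φ(1.96√(1 + v) − 2.80), where 2.80 = 1.96 + 0.84
- type I error = 2[1 − Φ(1.96√(1 + v))]

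For k = 1: v = 2/3 × 1/3 × 1 = 0.222; √1.222 = 1.106; 1.96 × 1.106 = 2.167; 2.167 − 2.80 = −0.63; power 0.737.

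| Shift k | v | Interval width ratio | Power without centre | Type I error, exact balance |
|---|---|---|---|---|
| 0.25 | 0.0139 | 1.007 | 79.6% | 4.8% |
| 0.5 | 0.0556 | 1.027 | 78.5% | 4.4% |
| 1.0 | 0.2222 | 1.106 | 73.7% | 3.0% |

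**Range over the Italian share.** For p = 1/2 the three powers are 79.6%, 78.3% and 72.9%. For p = 4/5 they are 79.7%, 78.9% and 75.5%.

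**Simulation with partial blood consent.** If only some infants give blood, balance within centre is approximate. The simulation used 4,000 trials per setting, three centres of 200 infants and blocks of 4. Power without against with centre, for k = 0.25, 0.5 and 1.0, was:

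- half giving blood: 78.9 v 79.2%, 77.8 v 79.2%, 71.8 v 78.9%
- a quarter giving blood: 79.7 v 80.3%, 77.6 v 78.8%, 73.1 v 80.7%

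Type I error without centre was 5.0%, 4.4% and 4.3% with half giving blood, and 5.5%, 4.9% and 4.5% with a quarter. The Monte Carlo standard error is about 0.65 points for power and 0.34 for type I error. The unadjusted test therefore shows no clear inflation. It is conservative under exact balance and close to nominal when balance is only approximate.

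**The case against.** The strongest objection is that the covariates for one secondary titre in a subgroup are normally settled in the statistical analysis plan, which is not shown, and that nothing in the protocol forbids centre. Section 14.1 names ANCOVA, leaves its confounder list open and starts its final regression from unspecified core variables. Section 6.4.1 lists immunisation. Section 12.8 says in whom antibodies are measured, not that titres are pooled in one test. The pooling follows from the general wording of section 14, which covers every interval outcome.

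Much of this stands, and it is why the point is minor. It does not remove the point. The protocol does state tests for interval data, and those tests ignore the stratum. The adjustment promised in 10.4 is, on its wording, for factors other than centre. Differences from an earlier visit (14.3.1) do not help either, because blood is drawn only at 6 and 12 months, so there is no sample from before the first dose. A centre term could serve other outcomes too, but here the protocol itself shows that centre determines the exposure behind the measurement.

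Three stronger readings are tempting and are not supported:

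- **Bias in the formula comparison.** A reader might infer that mixing schedules biases it. Blocks of 4 within centre keep the schedules balanced between arms, feeding is blinded, and consent to blood sampling is sought at study entry (synopsis).
- **Centre discarded by model selection.** A reader might infer that the elimination step in 14.1 would drop centre. That rule is expressed as a change in an odds ratio, and the protocol does not state it for continuous titres.
- **Conflicting dose timing.** A reader might see a conflict between the last dose at 11 months (12.8) and week 44 in the schedule table (12.12). The table counts four-week months for every HEXAVAC dose. The entry is the same in both arms and does not affect the comparison.

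**Conclusion.** The point holds as a low-severity improvement. One subgroup contains three-dose and four-dose infants, centre determines which, randomisation is stratified by centre, and the stated interval-data tests have no centre term. The formula comparison remains unbiased.

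The loss is negligible for a shift of 0.25 SD, about 1.5 points of power at 0.5 SD and about 6 points at 1 SD (80% to 73.7%), where the interval is 10.6% wider. All of this rests on an assumed schedule shift, Italian share and 80% reference power. The protocol does not say which shift applies. The primary endpoint and the sample size are not touched.

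**What to change.** State that the 12-month HEXAVAC antibody response is compared between the formula groups on log titre, by a linear model with formula group and centre as fixed factors, and that centre is always kept in the model. Because the two Italian centres share one schedule and the German centre has the other, the centre factor also absorbs the schedule difference.

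The cost is one model term in a secondary analysis, with no extra infants, samples or visits. The protocol already allows log transformation and ANCOVA, so no new method is needed.

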## 12.9 Special recheck of feeding group

At the infant's age of 8 weeks the feeding regimen of infants in the formula groups are rechecked with special importance. Only those formula infants who reached full formula feeding will be evaluated in the per-protocol analysis as formula infants, those who are still on partial breastfeeding as mixed formula infants. Similarly, infants recruited on full breastfeeding will be rechecked with special importance at 4 months if they are still on full breastfeeding to be evaluated later on as fully breastfed infants. Final recheck of adherence to feeding regimen is at study end.

